**Inclusion criteria**

- Hong Kong Chinese
- Age at enrolment: 4-12 years
- Myopia (in spherical equivalent refraction, SER)  $-0.75\text{D}$  or below in both eyes
- Documented evidence of fast progressing myopia in the last 2 years, either in SER or axial length (AL) (Details in Section 5.1):
  - SER progression:  $0.50\text{D}/\text{year}$  or more in either one eye or both eyes
  - AL elongation:  $0.27\text{mm}/\text{year}$  or more in either one eye or both eyes
- For children aged 4-6 years without past prescription forms, eligibility requires myopia below the 3rd percentile on refraction curves:
  - 4-5 years old: myopia of  $-0.75\text{D}$  or below in both eyes
  - 6 years old: myopia of  $-1.25\text{D}$  or below in at least one eye, with the other eye  $-0.75\text{D}$  or below
- Best-corrected visual acuity (BCVA) in both eyes matches age norms:
  - 4-6 years old:  $0.20 \log\text{MAR}$  (or its equivalent) or better
  - 7-12 years old:  $0.00 \log\text{MAR}$  (or its equivalent) or better
- Anisometropia of  $1.50 \text{ D}$  or less.
- Astigmatism of  $2.00 \text{ D}$  or less.
- Acceptance of random group allocation and the masked study design
- Able to wear the prescribed spectacle full-time

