#### **5.4. Potential risks**

The eye examination should not result in any undue discomfort. A mild stinging sensation may be experienced for a few seconds when the eye drops for refraction are instilled. The subject may also experience blurry near vision and sensitivity to bright light for about 24 hours after the instillation of eye drops. Therefore, it is suggested to wear sunglasses or a hat while going outdoors. An information sheet regarding the eye drops used in the study will be provided to participants.

The treatment interventions, specifically the spectacle, may induce blurriness, dizziness, and interrupted binocular vision at the first few days of lens wear. A one to two weeks' adaptation period may be required until the symptoms resolved. Upon experiencing persistent discomfort while wearing the spectacle, subjects or parents should report to the Investigators via phone call or message ([name] or [name], [contact]).

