### **5.9. Withdrawal criteria**

Subjects (or parents/guardians for subjects <18 years of age) are free to withdraw from participation in the study at any time upon request. No further data will be collected on subjects who withdraw from this study.

If significant intolerance to the treatment intervention is suspected at any time after randomisation, subjects can choose to withdraw or terminate treatment (either treatment or control group).

An Investigator may discontinue or withdraw a subject from the study for the following reasons:

- Significant study intervention noncompliance: unable to contact via 3 phone calls and 3 messages, more than 3 attempts to arrange missed follow-up appointments, wearing the spectacles less than 5 days a week and/or an average of less than 5 hours/day.
- If any clinical adverse event or situation occurs (e.g., allergies to eye drops, reduction of visual function such as diplopia, reduction of BCVA; subject to clinicians' judgement) such that continued participation in the study would not be in the best interest of the subject.

- If the participant meets an exclusion criterion (either newly developed or not previously recognized) that precludes further study participation.

Should subjects require discontinuation of treatment intervention for any reason, follow-up visits and data collection will not continue as scheduled. The reason for discontinuation or withdrawal from the study will be recorded on the Discontinuation/Withdrawal Case Report Form (CRF) in a web-based secure remote electronic database named Research Electronic Data Capture (REDCap). Subjects who signed the informed consent form and were Randomised but did not receive treatment intervention may be replaced. If there are subjects who signed the informed consent form, were Randomised, received the study intervention but were discontinued or withdrawn within the first month due to not meeting inclusion criteria (e.g., unable to tolerate spectacles or eye drops), and it is still within the recruitment period, then these participants' randomisation will be discarded and replaced with a participant from the next allocation. All spectacles (used or unused) will be returned to the unmasked Investigator upon withdrawal or discontinuation from the study.

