### 6.2. Statistical analysis

Data from the right eyes will be used for analyses when both eyes show fast progression. If only one eye demonstrated fast progression, that specific eye would be used for analyses. Demographic and optometric data will be displayed as mean and standard deviation, or number and percentage as appropriate. The Chi-square test (or if appropriate, Fisher's Exact test) and unpaired t-test will be performed to compare baseline between-group differences in demographics (age, sex). Myopia progression will be calculated as the difference between SER and AL at the baseline, the 6-month and the 1-year visits, respectively.

The unpaired t-test will be used to compare the changes in primary and secondary outcomes between groups. The efficacy of myopia control of DIMS lens will be determined by dividing the difference in myopia progression (or axial elongation) between two groups with the myopia progression (or axial elongation) in the SV group, then multiplied by 100%. Multiple regression analysis will be employed to identify factors that may be associated with myopia control efficacy. Regarding visual performance and comfort, subjective ratings collected by questionnaires will be compared between groups using Mann-Whitney U test.

Treatment will be discontinued if any treatment-related adverse event arises, such as constant visual disturbance (e.g., ghosting, diplopia, glare, etc.). The number of subjects

discontinuing treatment prematurely for any reason will be summarised by reasons for discontinuation. The incidence of all serious adverse events will be summarised.

Data analysis will follow an intention-to-treat approach. Missing values of outcome variables and covariates will be replaced using multiple imputation procedures with 10 sets of imputations assuming missing at random. All analyses will be 2-tailed with a significance level of 2.5%.

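### Section 5.9 discards the randomisation of treated children who stop in the first month, which contradicts the stated intention-to-treat analysis

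*Protocol*

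**What the plan says.** Section 5.9 of the protocol contains two replacement rules.

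- Before treatment: children who were "Randomised but did not receive treatment intervention may be replaced".
- After treatment: children who were randomised, received the study lenses and were "discontinued or withdrawn within the first month due to not meeting inclusion criteria (e.g., unable to tolerate spectacles or eye drops" have their "randomisation will be discarded and replaced with a participant from the next allocation". This applies only if "it is still within the recruitment period".

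The second rule appears to lean on the inclusion criterion "Able to wear the prescribed spectacle full-time" (Overview, Inclusion criteria; repeated in substance in section 5.1).

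On analysis, section 6.2 states: "Data analysis will follow an intention-to-treat approach". The Overview says the same. Missing outcomes are to be filled by "multiple imputation procedures with 10 sets of imputations assuming missing at random". Neither place says whether a child whose randomisation was discarded stays in the analysis set.

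On early symptoms, section 5.4 states: "The treatment interventions, specifically the spectacle, may induce blurriness, dizziness, and interrupted binocular vision at the first few days of lens wear". It allows one to two weeks for adaptation.

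**The concern.** Intention-to-treat means that every randomised child is analysed in the arm to which chance assigned the child. Section 5.9 removes some of these children after they have worn the assigned lens, for a reason that the lens itself may cause. The remaining arms are then no longer the arms that randomisation created, and the primary D2 versus SV comparison loses part of the protection that randomisation gives.

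Later analysis cannot fully repair this. A child who is discarded and not followed has no 12-month refraction. Substituting the next entry on the list does not restore the lost comparison either: the replacement is a different child who has not been selected in the same way, and section 5.9 does not say that the next allocation must be to the same arm.

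**Working it through.** **Is the trigger an eligibility failure?** The sequence in the protocol is:

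1. Randomisation takes place at V1, after the baseline measurements (Overview, Randomisation; sections 5.16 and 5.17.1).
2. Lenses are dispensed at V2, with a target of day 30 and a window of days 15-45 (section 5.15). Section 5.9 does not say when its month starts. Because it requires that treatment was received, I read it as the first month of wear.
3. Spectacle tolerance can therefore be observed only after randomisation and after dispensing. The adaptation period in section 5.4 falls inside that month.
4. Eye-drop intolerance is the other example. Cycloplegia is scheduled at V1 and next at V4 (section 5.16), so during the first month of wear the spectacles are the more likely practical trigger.

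Spectacle intolerance is thus a post-randomisation event that can depend on allocation. Ability to wear the lenses full-time can be judged before randomisation only as an expectation.

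**The plan's own figures.** Section 6.1 gives a difference of 0.315 D, SD 0.475 D, stated effect size 0.658, and 50 and 59 per group at two-sided alpha 0.05 and 0.025 with 90% power. A two-sample t-test calculation at effect size 0.658 gives 49.5 and 58.6, which round up to 50 and 59. The 65 per group follows as 59 × 1.1 = 64.9. The present point does not rest on these figures.

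**Illustration of size.** The protocol gives no intolerance rate. Let f be the share of D2 children discarded. Assume that they gain no benefit, that retained D2 children show the planned 0.315 D, and that no SV child is discarded.

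- Difference with all randomised children kept = 0.315 × (1 − f)
- Overstatement after discarding = 1/(1 − f) − 1
- Power = Φ(difference / (0.475 × √(2/59)) − 2.241), a normal approximation at alpha 0.025 with 59 per group

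| f (assumed) | Children out of 65 | Difference, all kept (D) | Overstatement | Power |
|---|---|---|---|---|
| 0% | 0 | 0.315 | 0% | 91.3% |
| 2% | 1.3 | 0.309 | 2.0% | 90.1% |
| 5% | 3.2 | 0.299 | 5.3% | 88.1% |
| 10% | 6.5 | 0.284 | 11.1% | 84.1% |
| 15% | 9.8 | 0.268 | 17.6% | 79.4% |

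**Selection by prognosis.** Discarding also shifts the comparison if the discarded children would have progressed differently anyway. Let m be their mean progression minus that of retained children, and g the share discarded in SV. The shift in the D2 minus SV difference is −(f − g) × m. For an assumed m of ±0.2 D, f = 10% and g = 0, it is 0.02 D in either direction. For f = g it is zero. This component has no predictable sign.

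**The case against.** Several points on the other side have force.

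- **The rule is limited.** It applies only while recruitment is open, it covers eye-drop intolerance, which has no evident link to lens type, and it is worded as an inclusion failure. This narrows its reach but does not remove the contradiction for a child who stops because of the spectacles.
- **Unequal intolerance is not shown.** A reader might infer from section 5.4 that D2 will lose more children than SV. That section does not separate the lens types, and section 5.9 provides for intolerance in either group. Unequal loss is plausible but remains an assumption.
- **Direction.** A reader might infer that the rule favours the better-tolerated arm. The arithmetic points the other way: discarding hides failures, so the arm with more intolerance would most plausibly gain.
- **Safety reporting.** A reader might infer that early intolerance vanishes from the record. It does not. Section 5.9 records the reason for stopping on a case report form, section 6.2 summarises discontinuations by reason, and section 8.5 requires all adverse events to be documented. What is unclear is whether discarded children count in the denominator.
- **Masking.** Unmasked investigators dispense the lenses (section 5.6.1), and section 5.9 names no masked person to decide who is discarded. That is a gap. The protocol does not support the inference that knowledge of the lens would drive the decision, and families are masked.
- **Deleting the sentence alone would not recover the gap shown in the table.** This objection stands. Section 5.9 also ends scheduled data collection once treatment is discontinued. Retained children would then have only outcomes imputed under missing at random. If the imputation model includes arm, which the protocol does not specify, D2 children would be imputed near the retained D2 mean and the estimate would stay close to 0.315 D.

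**Conclusion.** The contradiction between section 5.9 and section 6.2 is established from the text alone and needs no assumption about rates. A post-randomisation event that may depend on the lens is treated as an eligibility failure, and the child's allocation is erased.

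The size and direction of the resulting bias are unknown. The 5-11% overstatement at 5-10% discarded is an illustration. It rests on three assumptions: the D2 rate, no discards in SV, and no benefit in discarded children. It should not be read as a forecast that the D2 result will be inflated by that amount. If intolerance does turn out to be more common with D2, flattering D2 is the most plausible direction. The rule should be amended whatever its size, because the data of discarded children cannot be recovered afterwards.

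**What to change.** Amend section 5.9 as follows.

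1. Delete the rule that discards and replaces the randomisation of treated children.
2. State that every randomised child stays in the intention-to-treat set under the allocated arm, including children who never received lenses.
3. If further children are enrolled to cover losses, count them as additions with their own allocation and not as substitutes. This applies to both replacement rules.
4. Allow exclusion after randomisation only for ineligibility established from data collected before randomisation, judged by someone masked to allocation.
5. Reconcile section 5.9, which ends scheduled follow-up after discontinuation, with section 8.5, which requires follow-up visits for trial assessment when an adverse event leads to stopping. The outcome determines whether retained children have observed or only imputed 12-month values.

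The cost is a short amendment. The estimate may be slightly less favourable, and some outcomes will either be missing or need follow-up visits.

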#### **5.10. Lost to follow-up**

A subject will be considered lost to follow-up if they fail to return for at least one of the data collection visits and is unable to be contacted by study staff. The following actions must be taken if a subject fails to return to the research clinic for a required study visit:

- The Investigators will attempt to contact the subject and reschedule the missed visit within 2 weeks of the original schedule and counsel the subject on the importance of maintaining the assigned visit schedule and ascertain if the subject and their family wishes to and/or should continue in the study.
- Before a subject is deemed lost to follow-up, the Investigator will make every effort to regain contact with the participant (where possible, 3 telephone calls and 3 messages, if necessary, a letter to be sent to the participant's last known mailing address or email). These contact attempts will be documented in the subjects' study file.
- Should the subject continue to be unreachable, they will be considered to have withdrawn from the study with a primary reason of lost to follow-up.

### 5.11. Baseline and eligibility assessment

All data will be collected via face-to-face meetings with Investigators at the Optometry Research Clinic of School of Optometry in PolyU. The following data will be collected at the baseline and eligibility assessment according to the manual of procedures.

- **Demographic data:** ethnicity, age (date of birth) and gender.
- **Concomitant medication:** information about types and dose of medications or supplements currently used (will be asked at all visits).
- **Allergies history:** information about any allergies to medication or others (will be asked at all visits).
- **Questionnaire:** information about the participants' visual habits and parental history of myopia.
- **Presence of strabismus:** measured using the cover test at distance and near.
- **Autorefraction and keratometry:** measured using a Shin-Nippon NVision-K 5001 open-field autorefractor.
- **Pupil size:** measured using VIP-300 Pupillometer under photopic condition.
- **Subjective refraction:** measured using trial frame and loose lenses (most plus before blur), Jackson cross cylinder for astigmatism and Thomson Test Chart 2000 system.
- **Objective refraction:** measured using retinoscopy, trial frame and loose lenses and Thomson Test Chart 2000 system.
- **BCVA:** High contrast BCVA measured monocularly and binocularly at distance and near using the logarithmic visual acuity charts "ETDRS". Low contrast BCVA measured binocularly at distance using the 10% Michelson low contrast logarithmic visual acuity charts "ETDRS".
- **Binocular vision with dry subjective refraction:** stereopsis measured using a Randot test, monocular and binocular amplitude of accommodation measured using a RAF ruler, monocular accommodative lag measured with a 3D stimulus using a Shin-Nippon NVision-K 5001 open-field autorefractor, and phoria measured using a Howell Phoria Card at distance and near.
- **Intraocular pressure (IOP):** IOP will be measured by Topcon CT-80 non-contact tonometer or ICare tonometer.
- **External ocular health examination:** using a slit lamp biomicroscope.

- **Cycloplegia:** One drop of Alcaine 0.5% or Provan 0.5% (topical anaesthetic) and 1 drop of Cyclopentolate hydrochloride 1.0% (antimuscarinic eye drop) will be instilled to induce cycloplegia. The effect of the cycloplegia will be evaluated by means of amplitude of accommodation (push-up method); if the amplitude of accommodation is more than +2.00D, then a second drop of 1% Cyclopentolate will be instilled. The remaining tests of this section will be performed under cycloplegia.
- **Cycloplegic autorefraction:** same procedure as the non-cycloplegic autorefraction.
- **Peripheral refraction:** measured by using a Shin-Nippon NVision-K 5001 autorefractor at center, 10°, 20° and 30° of the nasal and temporal visual field across the horizontal meridian in the right eye (if both eyes confirm fast progress) or in the fast-progress eye (if only 1 eye confirmed fast progress). Five measurements will be taken and averaged.
- **Cycloplegic subjective refraction:** same procedure as the non-cycloplegic subjective refraction.
- **Axial length:** measured by ZEISS IOLMaster 500.
- **Dilated fundus ophthalmoscopy:** posterior eye health will be checked using a binocular indirect ophthalmoscopy and fundus photo camera.

#### 5.12. Primary outcome measure

The primary outcome will be the change in SER from baseline to 12 months, as measured by cycloplegic autorefraction (Shin-Nippon open-field autorefractor) in both eyes.

#### 5.13. Secondary outcome measure

The secondary outcome measure is the change in AL under cycloplegia from baseline to 12 months.

#### 5.14. Other outcome measures

- **Choroidal thickness:** measured using a Topcon DRI OCT Triton optical coherence tomography at spectacle dispensing, 1 month after spectacle dispensing, 6, 12, 13 (for control group crossover to D2 group), 18, 24 months.
- **Corneal curvature:** measured at 6, 12, 18, 24 months.

- **Peripheral refraction:** at centre, 10°, 20° and 30° of the nasal and temporal visual field across the horizontal meridian in right eye at 6, 12, 18 and 24 months.
- **Heterophoria:** measured at 6, 12, 18, 24 months.
- **Pupil size:** measured in normal lighting conditions at 6, 12, 18, 24 months.
- **Amplitude of accommodation (binocular and monocular, with trial frame):** measured at 6, 12, 18, 24 months.
- **Accommodative lag (with trial frame):** measured with a 3D stimulus at 6, 12, 18, 24 months.
- **IOP:** measured at 6, 12, 18, 24 months
- **Visual performance questionnaire:** measured at 1 month after spectacle dispensing and 1 month after control group crossover to D2 group.
- **Treatment compliance:** spectacle lens wear duration per day and number of days per week monitored at 1 month after spectacle dispensing, 6, 12, 18, 24 months.
- **Adverse events and device events:** Information regarding to any adverse events and whether they are related to the active treatment will be collected at all the time points.

All other measurements will be classified as exploratory outcomes.

**5.15. Study visits time windows**

| Visit Number                    | Target Visit Window (days) | Acceptable Visit Window (days) |
|---------------------------------|----------------------------|--------------------------------|
| V1 (Baseline)                   | 0                          | 0                              |
| V2 (dispensing)                 | 30                         | 15-45                          |
| V3 (1-month after dispensing)   | 60                         | 53-67                          |
| V4 (6-month)                    | 180                        | 150-210                        |
| V5 (12-month)                   | 360                        | 330-390                        |
| V5a (dispensing)*               | 390                        | 375-405                        |
| V5b (1-month after dispensing)* | 420                        | 413-427                        |
| V6 (18-month)                   | 540                        | 510-570                        |
| V7 (24-month)                   | 720                        | 690-750                        |

\* Only applicable for control group

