## **Objective**

Primary:

- i. To determine the efficacy of D2 lens design in slowing myopia progression in children with fast progressing myopia as compared to the single vision (SV) control.

Secondary:

- i. To determine the efficacy of D1 lens design in slowing myopia progression in children with fast progressing myopia as compared to SV control.
- ii. To investigate if baseline RPR influences the outcome of myopia control when using DIMS lenses.
- iii. To determine if the change of choroidal thickness following short-term DIMS lens wear has a prognostic value in determining the efficacy of myopia control over one year.

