### 4. Study Objective

Primary:

- i. To determine the efficacy of D2 lens design in slowing myopia progression in children with fast progressing myopia as compared to SV control.

Secondary:

- ii. To determine the efficacy of D1 lens design in slowing myopia progression in children with fast progressing myopia as compared to SV control.
- iii. To investigate if baseline RPR influences the outcome of myopia control when using DIMS lenses.

- iv. To determine if change of choroidal thickness following short-term DIMS lens wear has a prognostic value in determining the efficacy of myopia control over one year.

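### The one-month choroidal scan may fall anywhere from 8 to 52 days after dispensing, and follow-up peripheral refraction can be taken in a different eye from baseline

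*Protocol*

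**What the plan says.** **Timing.** The table in Protocol section 5.15 sets V1 at day 0 and gives every other visit a target day and an acceptable window. V2, the dispensing visit, has target day 30 and window 15-45. The next row, "V3 (1-month after dispensing", has target 60 and window 53-67. For the control group's change to D2 lenses, V5a (dispensing) has target 390 and window 375-405, and "V5b (1-month after dispensing" has target 420 and window 413-427.

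Section 5.14 schedules choroidal thickness "at spectacle dispensing, 1 month after spectacle dispensing, 6, 12, 13 (for control group crossover to D2 group), 18, 24 months". The Objective part of section 1 (item iii) uses the early change as a predictor: "To determine if the change of choroidal thickness following short-term DIMS lens wear has a prognostic value" for one-year efficacy. Section 4 repeats this as item iv.

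**Eye.** For baseline peripheral refraction, section 5.11 specifies measurement "in the right eye (if both eyes confirm fast progress) or in the fast-progress eye (if only 1 eye confirmed fast progress". For follow-up, section 5.14 specifies measurement "across the horizontal meridian in right eye at 6, 12, 18 and 24 months", with no exception. Section 6.2 analyses the right eye when both progress fast, and otherwise: "If only one eye demonstrated fast progression, that specific eye would be used for analyses". Sections 1 and 5.1 admit children in whom only one eye meets the progression criterion. Section 1 lists the change in relative peripheral refraction among the other outcomes.

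**The concern.** Both outcomes are changes between two measurements, and in each the protocol does not hold constant something that the change depends on.

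For the choroid, it is the duration of lens wear. If the early scan follows about a week of wear in one child and more than seven weeks in another, differences between children in the choroidal change reflect exposure time as well as individual response. That adds noise to the predictor in a stated secondary objective and would tend to weaken any association with one-year efficacy. The visual performance questionnaire and the first compliance record fall at the same visit. Section 5.4 allows one to two weeks for adaptation, so an early V3 can fall inside that period and a late one cannot.

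For peripheral refraction, it is the eye. If baseline is the left eye and follow-up the right, the difference is not a change within an eye, and the follow-up eye is not the one analysed for SER and AL. Peripheral refraction is specified for one eye only, so a matching value cannot be recovered afterwards.

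**Working it through.** **1. Interval from dispensing to the one-month visit** (days from V1 = day 0, section 5.15)

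Target gap = later target - dispensing target. Minimum = lower limit of the later visit - upper limit of dispensing. Maximum = upper limit of the later visit - lower limit of dispensing.

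| Pair | Target gap | Minimum | Maximum |
|---|---|---|---|
| V2 to V3 | 60 - 30 = 30 | 53 - 45 = 8 | 67 - 15 = 52 |
| V5a to V5b | 420 - 390 = 30 | 413 - 405 = 8 | 427 - 375 = 52 |

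The targets reproduce the stated one month. The windows do not protect it: dispensing carries a tolerance of 15 days (30 - 15 and 45 - 30) and the later visit its own 7 days (60 - 53 and 67 - 60). Because both run from baseline, the tolerances add: 30 ± (15 + 7) gives 8 to 52. The ratio of the extremes is 52/8 = 6.5.

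The gap that is in window depends on the dispensing day:

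- Day 15: 53 - 15 = 38 to 67 - 15 = 52 days.
- Day 30 (target): 53 - 30 = 23 to 67 - 30 = 37 days.
- Day 45: 53 - 45 = 8 to 67 - 45 = 22 days.

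An exact 30-day visit needs 53 ≤ V2 + 30 ≤ 67, so V2 must fall on days 23 to 37. That is 15 of the 31 permitted dispensing days. On the other 16, a visit exactly 30 days after dispensing is outside the window. For V5a the corresponding days are 383 to 397.

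**2. Eye measured, by pattern of progression**

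| Fast eye(s) | Baseline (5.11) | Follow-up (5.14) | Analysis eye (6.2) | Same eye throughout? |
|---|---|---|---|---|
| Both | Right | Right | Right | Yes |
| Right only | Right | Right | Right | Yes |
| Left only | Left | Right | Left | No |

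The conflict is confined to children whose only fast-progressing eye is the left. Their share is not stated. For scale, each 10% of such children is 0.10 × 59 = 5.9 to 0.10 × 65 = 6.5, about 6 per arm, using the section 6.1 group sizes before and after the dropout allowance.

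**The case against.** **The 8 and 52 days are corner cases.** They need dispensing and scan at opposite edges of their windows. On-target dispensing gives 23 to 37 days, and the plan's intention of one month is clear. This is right, and the 6.5-fold ratio should be read as a ratio of extremes. It does not remove the defect: once dispensing is on day 45 or day 15, no in-window visit can be at 30 days.

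**The harm cannot be sized, and analysis could absorb it.** The protocol gives no time course for the choroidal response. Dispensing and V3 have their own record forms, so days of wear should be derivable, and adjustment could be left to an analysis plan. The first part stands: the loss of prognostic signal cannot be quantified here. Adjustment is useful for scans already taken, but is weaker than measuring at a common time.

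**The right-eye wording looks like a leftover.** The summary of changes records an update to peripheral refraction in 5.11 and none in 5.14, and the Manual of Procedures, which is not shown, may give staff the correct rule. That is plausible. The current sections still conflict, and under section 5.18 departing from the protocol without an amendment is a violation.

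**Little rests on the peripheral-refraction change.** It is an other outcome, and the secondary objective on relative peripheral refraction uses only the baseline value, taken in the intended eye. This stands and limits the importance.

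**The 5.11 eye rule is incomplete.** Children aged 4-6 may enter without past prescription forms, so some have no documented fast-progressing eye. This also stands, and the correction must cover it.

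**Conclusion.** Both defects hold as the protocol is written.

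- **Timing:** the permitted dispensing-to-scan interval is 8 to 52 days for both V2-V3 and V5a-V5b, against a stated one month. This rests on all window days being counted from V1, which the table's targets support. The actual spread depends on dispensing dates that the protocol cannot supply.
- **Eye:** followed literally, the change in relative peripheral refraction is not a within-eye change for any child whose only fast eye is the left. The number affected is unknown.

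The primary SER comparison, the secondary AL comparison and the baseline peripheral-refraction objective are untouched. The protocol names no eye for choroidal thickness, so the choroidal problem is one of exposure time only. The point should be corrected, but it does not threaten the main conclusion of the trial.

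**What to change.** - **Section 5.15:** count V3 from the actual V2 date and V5b from the actual V5a date, using the plan's own 30-day gap and 7-day tolerance. The permitted interval becomes 30 - 7 = 23 to 30 + 7 = 37 days.
- **Scans already taken:** use the actual number of days between dispensing and scan as a covariate in the prognostic analysis, and report its distribution.
- **Section 5.14:** replace the right-eye wording with the eye rule of section 5.11. State that one study eye is fixed and recorded at V1 and used for SER, AL and peripheral refraction at every visit.
- **Children aged 4-6 without past prescription forms:** state how the study eye is chosen when no progression record exists, since neither 5.11 nor 6.2 settles it.
- **Peripheral refraction already collected:** record which eye was measured at each visit. Where baseline and follow-up eyes differ, do not compute a change from them; report how many children are affected.

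The cost is wording in the protocol and the Manual of Procedures, with no added visit or measurement. The eye correction is the more urgent, because a follow-up eye that was not measured cannot be recovered.
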